## Abstract

**Abstract:**

**Introduction:**

Electronic Palliative Care Coordination Systems (EPaCCS) are electronic registers that aim to facilitate documentation and sharing of up-to-date information about patients’ end-of-life preferences and plans for care among different health services. They aim to improve patients’ experiences and outcomes and mitigate costs linked to undesired aggressive care. However, evidence on the equitable delivery of EPaCCS and the extent to which advance care planning (ACP) enhances end-of-life care remains sparse. This study aims to explore the effect of EPaCCS on healthcare outcomes, service utilisation, and costs. It will also estimate the association between social determinants of health and the content and use of EPaCCS.

**Methods and analysis:**

The PREPARE project is a retrospective observational cohort study conducted in two phases. We will analyse routinely collected data from three EPaCCS registers from London, Bradford and Leeds. The first phase will use descriptive analysis to describe the completeness of EPaCCS, the content of EPaCCS, and socio-demographic and clinical characteristics of individuals with EPaCCS, and will model the relationship between social determinants of health and completion of ACP components and the creation of EPaCCS. The second phase will use a natural experiment to compare quality indicators (place of death and hospital use) between individuals with EPaCCS and those without. The control groups will be identified through the Leeds decedent dataset and through linking the London EPaCCS register to an electronic record used in North West London. Also, we will quantify healthcare costs and outcomes.

**Ethics and dissemination:**

Research approval has been secured from the Health Research Authority (ref 24/LO/0194), London - South East Research Ethics Committee (ref 24/LO/0194) and Confidentiality Advisory Group (ref 24/CAG/0046). Dissemination of findings will occur through peer-reviewed publications, knowledge exchange events and collaborative efforts with patient and public involvement partners.

STRENGTHS AND LIMITATIONS OF THIS STUDYInclusion of all Electronic Palliative Care Coordination Systems (EPaCCS) records in London (2010–2022), Leeds (2015–2023) and Bradford (2015–2023) with an additional cohort of patients without EPaCCs for Leeds (2021–2023) and London makes this the largest collection of data sources in an EPaCCS UK study.Following the ‘nothing about us without us’ philosophy, there is strong patient and public involvement collaboration at every stage of the project.A natural experiment aims to provide credible causal estimates of EPaCCS effects on end-of-life outcomes, which will strengthen the evidence base.Recommendations to key stakeholders based on the findings will inform future EPaCCS use.Challenges comparing EPaCCS due to the interoperability of the data may limit the generalisability of the findings to other EPaCCs within the UK.

## Introduction

 Over 530 000 people die each year in the UK^1^ and this number is increasing.^2^ Many of these deaths are associated with people living with multiple morbidities and complex end-of-life care issues.^3^ The National Health Service (NHS) should provide high-quality, safe, person-centred end-of-life care consistent with their wishes.^4^ Most people wish to die at home.^5 6^ Additionally, hospital was the least preferred place of death for patients receiving palliative care in three countries.^6^ However, more than half of UK people currently die in hospital^2^ and many experience unplanned hospital admissions, including emergency department visits and unwanted and futile aggressive treatment.^27^,^9^ Failure to address these critical issues undermines the realisation of benchmarks that define a good death, as perceived by individuals, their families and healthcare providers alike.^10^,^12^

Advance care planning (ACP) is a voluntary process that supports adults in considering and sharing their values, goals and preferences regarding future care, including location of death so that if they lose mental capacity to make informed decisions for themselves, health professionals and their families can provide care consistent with their wishes.^13^ In the UK, ACP is endorsed in national policy.^14^ Despite scepticism of its value,^15^,^17^ an intrinsic logic of ACP underpins its use in practice and justifies continued research. Potential ACP benefits include providing important opportunities for discussion of diagnosis and prognosis so care and treatment are aligned with individuals’ preferences, improving symptom discussions and treatment adherence and reducing misunderstandings and conflict between medical staff and families.^18^ ACP may also lead to fewer interventions of limited or futile clinical value, earlier access to palliative care, reduced inappropriate emergency hospital admissions, fewer hospital deaths and increased rates of hospice admission or appropriate care at home.^19^,^21^ ACP is thought to help families prepare for the death of a loved one, resolve family conflict and help with bereavement.^22^ Although primarily concerned with improving the appropriateness and quality of care, ACP may contribute to controlling important health spending and making more appropriate and considered use of scarce resources in end-of-life.^18 23^

*The NHS Long Term Plan* advises building a ‘digital front door’ connecting health professionals to people^24^ to improve access, coordination, health outcomes and efficiency.^25^ In line with this, ACP records need to be accessible to healthcare professionals across different settings.

Electronic Palliative Care Coordination Systems (EPaCCS) have been specifically designed to facilitate seamless electronic information sharing and enable ACP and end-of-life care decision-making to increase the likelihood of delivering end-of-life care following patient wishes and priorities.^26^,^28^ EPaCCS records are intended for creation by trained healthcare professionals with input from patients and their carers to enable patients to discuss and make decisions about their preferences for end-of-life care such as preferred place of death, the ceiling of treatment and resuscitation status. Once stored, it is expected that information should be shared electronically with different professionals across different settings to inform decision-making, especially in times of crisis (emergency services (NHS 111 and 999), general practice, specialist palliative care services, hospices, etc).^26 27^ Nationally, 175 (83%) clinical commissioning groups (CCGs), now Integrated Care Boards (ICBs), have either implemented EPaCCS or started planning for their implementation.^29^ The Department of Health’s National Commitment for End-of-Life Care has recommended continued EPaCCS roll-out^30^ and they have been endorsed in the ‘Palliative and End-of-Life Care: Statutory Guidance for Integrated Care Boards (ICBs)’.^31^

While EPaCCS offer potential merits, no UK research has yet evidenced (1) to what extent EPaCCS support advance care planning, (2) to what extent EPaCCS have been offered equitably to all those who stand to benefit from them, (3) the effect of EPaCCS on patients’ place of death, and (4) if EPaCCS are associated with the use of health resources at the end of life where care costs are high.^32^

The PREPARE study therefore aims to (a) describe the characteristics of people who receive EPaCCS to support decision-making at the end of life and to estimate the association between social determinants of health and the content of ACP contained within EPaCCS and (b) explore EPaCCS effect on healthcare outcomes, use and costs. Based on our findings, we will synthesise recommendations on the use of EPaCCS to support end-of-life care for people living with life-limiting illnesses and their families.

The study objectives are the following:

1A. To describe and categorise the data fields and completeness of data contained within each EPaCCS register.

1B. To describe the creation and content of EPaCCS records and elements relating to end-of-life decision-making preferences and ACP (ceiling of treatment, preferred place of care, and death and resuscitation status) in different regions across England.1C. To describe the socio-demographic and clinical characteristics of individuals who have created EPaCCS records in different regions across England.1D. To estimate associations between social determinants of health (socioeconomic position, ethnicity, age and gender) and the completion of elements of ACP within EPaCCS.1E. To estimate associations between social determinants of health (socioeconomic position, ethnicity, age and gender) and the creation of EPaCCS.2A. To explore the effect of EPaCCS on place of death and hospital use in the last 90 days of life.2B. To explore the effect of an EPaCCS record on healthcare costs in the last 90 days of life.

This HRA-approved protocol (V.1.1; January 2025) outlines in detail the motivation for this study, data sources, analysis plan, public and patient involvement, and ethical considerations.

### Methods and analysis

### Study design

Objectives 1A–1C will be addressed using descriptive statistics, objectives 1D and 1E using multivariable regression and objectives 2A and 2B using a natural experiment framework, which will allow us ultimately to make conclusions and recommendations about the continued use of EPaCCS.^33 34^ Descriptive statistics and multivariable regression are key tools in quantitative end-of-life research where there is a high reliance on routine data.^35^ However, these methods are not always reliable for generating credible causal estimates of treatment effects.^36^ Provided underlying assumptions are met,^37^ natural experiments can generate causal evidence from observational data, including routinely collected data. These have been little used in end-of-life care research to date,^38^ but may be particularly impactful in a field where randomised trials are infrequent and methodologically challenging,^39^ reliance on routine data is paramount^40^ and selection bias in routine data is a persistent concern.^41^

This evaluation of EPaCCS encompasses two distinct work packages that draw upon data from various routinely collected sources, and it is planned to be completed between 2024 and 2025. The first work package (WP1) will enable a comprehensive evaluation of the structure and completeness of three EPaCCS registers (London, Leeds and Bradford), the creation and content of EPaCCS records, exploring the social determinants of health of individuals with EPaCCS records and their association with the completion of elements of ACP within EPaCCS, and exploring the association of social determinants of health with EPaCCS creation. The second work package (WP2) will evaluate the benefits of care for individuals with EPaCCS records against those without. Additionally, it will investigate to what extent EPaCCS lead to better utilisation of scarce health resources. While the analysis of the two work packages will be conducted separately, understanding the content and structure of the datasets and the completeness of the data fields for the WP1 objectives will inform further analyses in WP2. Additionally, understanding which social determinants of health are associated with the creation of EPaCCS records will improve the analysis of WP2 by understanding how these variables should be treated in the statistical models. Together, the findings of WP1 and WP2 will provide evidence as to whether EPaCCS offer benefits to patients at the end of life, their families and the NHS. The study will derive high-quality evidence on factors influencing the uptake of EPaCCS, as well as the effect of EPaCCS on the costs and quality of end-of-life care.^42^

### Data sources

The study will use non-identifiable data from three EPaCCS across three distinct geographical locations in the UK, namely London, Leeds and Bradford, which combined have a population of 10.4 million people. These EPaCCS were introduced at different times within the same city and across different cities. This has led to natural variation in exposure, resulting in datasets that cover varying time periods: 2010–2022 in London, and 2015–2023 in Leeds and Bradford. Nonetheless, these EPaCCS are well established and contain a sufficient number of records, as illustrated in table 1, to enable meaningful individual site analyses and answer our research questions. Additional anonymised EPaCCS data from different regions will be considered if made available during the study. The sample size will be determined by the data available in the three datasets and will vary depending on the analysis.

**Table 1 T1:** EPaCCS and data availability

EPaCCS location	EPaCCS specific data
London EPaCCS	Coordinate My Care (CMC) served as the commissioned EPaCCS in London from 2010 to 2022, during which time it was also the largest UK EPaCCS. Covering 32 CCGs serving a population of 8.9 million, this EPaCCS dataset reflects a diverse urban patient population in terms of diagnosis, ethnicity and socioeconomic background. CMC records comprise data from various healthcare settings, including primary and secondary care, hospices and nursing homes. The dataset encompasses demographics, diagnoses, care preferences, the ceiling of treatment, resuscitation status, living circumstances, prognosis, performance status, date and place of death. Additionally, data is available regarding how often the record was accessed by urgent and non-urgent healthcare workers. In later years, patients had the option of starting a ‘MyCMC’ plan, whereby they use a patient portal to input some data themselves. The anticipated numbers for inclusion in the dataset are 140 000 records, of which 100 000 are for deceased patients.
North West London dataset	CMC records will be linked with the ‘Whole Systems Integrated Care’ (WSIC) dataset. WSIC is an electronic record used by healthcare professionals in North West London, which has a population of 2.4 million, to document essential information about patient care in the region (eight health boroughs, previously defined as CCGs).^65^ The WSIC dataset will include all individuals who have died in North West London within the timeframe spanning from 2010 to 2023. This linkage will allow the creation of two cohorts for comparison: individuals with EPaCCS (CMC) and those without EPaCCS. All decedents with a CMC record within the WSIC catchment area will be identified for inclusion within the linked dataset, while decedents without such records will form the control group. The WSIC dataset includes coded primary, secondary, acute, mental health, community health and social care data. This dataset also includes detailed information on social determinants of health, including ethnicity, and mortality data, including place of death. Cost data is also available as patient-level costs referring to the indicative spend calculated separately for each patient for each healthcare sector. This will be used in a cost minimisation analysis of EPaCCS, and it includes primary care level, acute, community, mental health and social care costs. Data linkage will be carried out by North West London Integrated Care Board and supported by existing data sharing framework.^66^ Figure 1 illustrates the data flow and linkage process. The linked dataset will be de-identified prior to being made available to the research team for the analysis
Leeds EPaCCS	The Leeds EPaCCS dataset represents a combined dataset from community palliative care providers that includes all primary care practices and two city hospice sites (St Gemma’s Hospice and Wheatfields Hospice) and limited secondary care data (eg, unplanned hospital admissions in the last 90 days of life). This dataset encompasses decedent patient records spanning from 2015 to 2023. It includes linked healthcare records data including primary and secondary care data, such as hospital admissions and diagnosis of severe mental illness or learning disability. The EPaCCS in Leeds covers the entirety of the former Leeds CCG serving a population of around 870 000 people through 94 general practitioners (GP) practices. Since 2019, approximately 50% of all people who die in Leeds have an EPaCCS.^67^ Data for all deaths across Leeds from 2021 to 2023 are also available, including decedents without EPaCCS. This will enable comparative analysis between patients with or without EPaCCS records. The anticipated number of records for inclusion is 15 500 decedent records.
Bradford EPaCCS	The Bradford EPaCCS dataset is collected and shared among healthcare providers (including both NHS and voluntary sector providers) through electronic health records. This dataset includes decedent patient records spanning from 2015 to 2023. This EPaCCS is commissioned across the Bradford and Airedale districts, serving a combined population of 585 000 with approximately 4800 deaths per year. Approximately 48% of all deaths in this area had an EPaCCS record in 2018/19.^68^ The anticipated number of records for inclusion is 17 000 decedent records.

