The study will describe how EPaCCS are used, specifically who creates EPaCCS records and what information they encompass regarding individuals’ preferences for end-of-life care. The study will describe data fields across each of the three datasets and evaluate their completeness. Additionally, a descriptive analysis of the three EPaCCS datasets will be undertaken to describe the creation and content of the records across the three regions. These specific regions were chosen for being large metropolitan areas with varied levels of material deprivation and a high concentration of ethnic minority groups. This analysis will focus on the elements of ACP used to support decision-making at the end of life, which include documentation of the ceiling of treatment, resuscitation status, preferred place of care and preferred place of death. The study will also explore if changes are made to decision-making over time for each of these elements. As the three EPaCCS in the study contain data from different periods in time, we will take into account the different timescales during the analyses. The uptake of EPaCCS will be evaluated by describing the number of records created across different time periods and locations. The study will also investigate the setting of the initial record creation (hospital care, primary care, community care). Furthermore, the study will describe the clinical characteristics of patients such as their diagnosis, performance status, capacity for decision-making, living arrangements and expected prognosis. The study will also describe their socio-demographic characteristics with a particular emphasis on social determinants of health such as age, gender, socioeconomic position and ethnicity. The socioeconomic position will be defined using the Index of Multiple Deprivation (IMD), a standard scoring system based on a range of economic, social and housing data, creating a single deprivation score for each small area of the country. Using methodology previously employed in studies by the research team,^43 44^ an IMD score will be created for each patient based on their postcode which will reflect the deprivation data for the Lower-layer Super Output Area (LSOA) within which the postcode falls. Moreover, the study will investigate across sites the association between social determinants of health and the completion of each of the four previously mentioned ACP elements. Table 2 shows the mapping of the study objectives to data sources and eligibility criteria. Exclusion criteria for all data sources are participants who have chosen National Data Opt-Out and those who have withdrawn consent.

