
**Table 2 T2:** Mapping study objectives to data sources and eligibility to be included in analyses

Objectives		Data sources and eligibility
Work package 1		
1A	To describe and categorise the data fields and completeness of data contained within each EPaCCS register.	Anonymised EPaCCS data from London (CMC, n=140 000), Leeds (n=15 500) and Bradford (n=17 000)
1B	To describe the creation and content of EPaCCS records and elements relating to end-of-life decision-making preferences and ACP (ceiling of treatment, preferred place of care, and death and resuscitation status) in different regions across England.	
1C	To describe the socio-demographic and clinical characteristics of individuals who have created EPaCCS records in different regions across England.	
1D	To estimate associations between social determinants of health (socioeconomic position, ethnicity, age, and gender) and the completion of elements of ACP within EPaCCS.	
1E	To estimate associations between social determinants of health (socioeconomic position, ethnicity, age, and gender) and the creation of EPaCCS.	WSIC-CMC dataset of North West London deceased patients with/without EPaCCSLeeds decedent dataset 2021–2023 of deceased patients with/without EPaCCS
Work package 2		
2A	To explore the effect of EPaCCS on place of death and hospital use in the last 90 days of life.	WSIC-CMC dataset of North West London deceased patients with/without EPaCCSLeeds decedent dataset 2021–2023 of deceased patients with/without EPaCCS
2B	To explore the effect of an EPaCCS record on healthcare costs in the last 90 days of life.	WSIC-CMC dataset of North West London deceased patients with/without EPaCCS

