### Analysis

The data from each of the three distinct EPaCCS will be analysed separately. Individual patient-level EPaCCS data will be accessed and cleaned for each of the three systems. The study will categorise the data into social determinants of health (age, gender, ethnicity, social deprivation), clinical characteristics and elements relating to ACP. The social determinants of health have been identified from existing literature for being associated with poor health experiences and outcomes. The study will assess the completeness of variables in the data, examining patterns of missing data at the individual level and identifying any outlier records. Based on the characteristics of missing data, the study will adopt an appropriate approach to treating missing data for statistical analysis. Several methods will be considered that are appropriate for missing at random and not missing at random data. Though, it is assumed that the missing mechanism will be missing not at random. However, no robust methods of imputing missingness in the independent variables with a missing not at random mechanism have been identified. If imputation was carried out, a sensitivity analysis will be conducted to compare parameter estimates with/without imputation. Missing values for key outcomes will be imputed using gender, age, comorbidity, cause of death, IMD and/or study area.^45^ For each ACP element, documented decisions will be categorised to create an outcome (binary or ordinal) variable for inclusion in logistic regression modelling of the relationship between each of these outcomes, as distinct analyses, and social determinants of health, adjusting for major confounding variables and consideration of random effects/fixed effects (eg, comorbidity). Confounders will be selected using expert knowledge, existing literature, and the completeness and availability of the data. Using the London and Leeds datasets, a dichotomised binary outcome of whether or not a patient has an EPaCCS record will be created for logistic regression, modelling the association between the creation of EPaCCS records and social determinants of health. The study will identify both similarities and differences between the creation, use and content of EPaCCS records in the three EPaCCS cohorts. Mindful of the reported challenges associated with the interoperability of EPaCCS data,^46^ the comparison of datasets will be cautiously approached. We will examine the impact of the significant increase in EPaCCS records in London,^47^ and potentially the two other cities, following the outbreak of COVID-19 in March 2020 in terms of the documentation and completeness of ACP elements within the EPaCCS records. We will carry out a secondary analysis (sensitivity analysis) excluding individuals whose records were created during the COVID-19 pandemic after examining the data and the trend in the creation of EPaCCS records.

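### For objectives 1A–1D, all 140 000 London records, 28.6% of them not counted as deceased, are compared with decedent-only Leeds and Bradford sets, so cross-register differences can reflect vital status rather than region

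*Protocol article*

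**What the plan says.** Under Data sources, Table 1 gives the London register as "140 000 records, of which 100 000 are for deceased patients". For Leeds it states "This dataset encompasses decedent patient records spanning from 2015 to 2023", and "The anticipated number of records for inclusion is 15 500 decedent records". The Bradford entry has the same form: "The anticipated number of records for inclusion is 17 000 decedent records".

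Table 2, which maps objectives to data sources and eligibility, gives one entry for objectives 1A to 1D: "Anonymised EPaCCS data from London (CMC, n=140 000), Leeds (n=15 500) and Bradford (n=17 000". The London figure is the full total, not the deceased subset. The work package 1 text sets no limit by survival: "Exclusion criteria for all data sources are participants who have chosen National Data Opt-Out and those who have withdrawn consent".

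The Analysis section of work package 1 says that each register is analysed separately. It goes on: "The study will identify both similarities and differences between the creation, use and content of EPaCCS records in the three EPaCCS cohorts". The work package 1 text also says that "the study will investigate across sites the association between social determinants of health and the completion of each of the four previously mentioned ACP elements". The outputs section intends the similarities and differences to inform future standardised systems.

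**The concern.** The three sets that the plan places side by side are not the same kind of population. Two contain only people who died. The third mixes people who died with people not counted as deceased. Completion of ACP elements, changes in decisions over time, performance status and expected prognosis may all differ between those two groups. If they do, London would differ from Leeds and Bradford even where documentation practice was identical, and the difference would be read as regional.

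Separate analysis does not remove this. Each register's own estimates are valid for the records it holds. The difficulty comes at the next step, when three sets of results are compared and regional variation is inferred. For objective 1D, the London associations describe a mixed population and the other two sites' associations describe decedents, so unequal coefficients need not mean unequal equity of practice.

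**Working it through.** **Inputs.** From Table 1: London 140 000 records, 100 000 of them for deceased patients; Leeds 15 500 and Bradford 17 000, all decedents. From Table 2: the same three totals, assigned to objectives 1A–1D. The two tables agree. The article gives no completion rates by vital status, so any difference in completion below is an assumption.

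**Share not counted as deceased.**
- London: 140 000 − 100 000 = 40 000, and 40 000 / 140 000 = 28.6%.
- Leeds and Bradford: 0%.
- All records in 1A–1D: 140 000 + 15 500 + 17 000 = 172 500, and 40 000 / 172 500 = 23.2%.

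**Effect on a London completion rate.** Let p_D be the completion rate in London decedents and p_N the rate in the other London records. Then

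London rate = (100 000 p_D + 40 000 p_N) / 140 000 = p_D + 0.286 (p_N − p_D).

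The shift away from the decedent rate is thus 0.286 times the difference in completion, in either direction:

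| Assumed difference, p_N − p_D | Shift in London rate |
|---|---|
| ±5 points | ±1.4 points |
| ±10 points | ±2.9 points |
| ±20 points | ±5.7 points |
| ±30 points | ±8.6 points |

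**Comparison with sampling error.** The margin for a difference of two proportions is 1.96 × √[p(1 − p)(1/n₁ + 1/n₂)].
- London (140 000) against Leeds (15 500): 0.83 points at p = 50%, 0.66 at p = 80%.
- London (140 000) against Bradford (17 000): 0.80 points at p = 50%, 0.64 at p = 80%.

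Even the smallest shift in the table, 1.4 points, exceeds these margins. At these sample sizes an artefact of that size would look like a clear difference.

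**Fields about death.** The London dataset includes date and place of death. If these fields are empty for the 40 000, their completeness over all London records cannot exceed 100 000 / 140 000 = 71.4%, however good the documentation. The decedent-only registers have no such ceiling.

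**Whether another provision covers this.** Three come near:
- The promise of caution in comparing datasets is tied to interoperability.
- The undertaking to allow for differing timescales concerns calendar periods.
- The COVID-19 sensitivity analysis excludes records by when they were created.

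None of them separates records by vital status. Objective 1E and work package 2 use deceased patients only, so within the plan it is London in 1A–1D that departs from a decedent population.

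**The case against.** The strongest reply is that the main analyses are within register. No pooled model, regional test or region effect is specified for 1A–1D, and the article lists difficulty in comparing registers among its limitations. The aim is to describe people who receive these records, and for that aim every London record-holder is a legitimate subject. Restricting 1D in London to decedents would condition on later death, discard 40 000 records and narrow the question to suit a limit of the other two extracts. Finally, a full statistical analysis plan is promised, and stratified reporting could be set out there.

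Much of this stands. It rules out making decedents the primary London population for 1B–1D as an obvious correction; that is a debatable trade-off. It does not answer the narrower point. Table 2 fixes which records are eligible, the cross-register description is planned in so many words, and the caution offered has a different reason. Eligibility does not prevent stratified reporting, but nothing in the article calls for it.

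A reader might also infer that the 40 000 are living patients with unfinished records, set against completed records in Leeds and Bradford. The documents do not support this. They say only how many records are for deceased patients; some deaths may be unrecorded. The London system was commissioned from 2010 to 2022, and nothing shows that these records were still being edited. The Leeds and Bradford records are called decedent records, not complete ones; their completeness is what objective 1A is to measure.

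**Conclusion.** The concern holds for cross-register statements under objectives 1A–1D. As written, the plan compares a London set with 28.6% of records not counted as deceased with two sets that have none, and differences can reflect vital status rather than region. Objective 1E, work package 2 and purely within-London description are unaffected.

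The counts are the article's own. The consequence rests on one assumption: that completion, content or the 1D associations differ by vital status. Neither the size nor the direction of that difference can be derived from the documents. It would therefore be wrong to state a fixed artefact of so many points; what can be stated is the rate of about 2.9 points in London completion per 10-point difference. For 1D, vital status may be related to age, one of the exposures, but the article gives no figure, and age is itself among the determinants being modelled.

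**What to change.** State in Table 2 and the work package 1 Analysis section that:

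1. All 140 000 London records are kept for description within London, including the inventory of data fields in 1A.
2. London results for 1A–1D, including completeness and the 1D associations, are reported by vital status.
3. Every statement comparing London with Leeds or Bradford uses the roughly 100 000 London decedent records.

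No new data are needed: the deceased count is already known and date of death is in the London dataset. The London n for cross-site statements falls from 140 000 to about 100 000, and the three-register total for them from 172 500 to 132 500. The loss of precision is small, because the smaller registers dominate the standard error. Against Leeds at p = 50%, 1.96 × √[0.25 (1/100 000 + 1/15 500)] = 0.85 points, compared with 0.83 before. The remaining cost is a little more analysis and reporting.
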